### Randomisation

Following collection of primary outcome data (child weight and length), ECEC services will be randomly assigned to the intervention or a usual care control group in a 1:1 ratio. Randomisation will be stratified by Aboriginal and Torres Strait Islander child enrolments (≥10%), to ensure equity of access and SES (dichotomised as high/low SES according to the SEIFA classification^39^ of the ECEC service postcode), given the association between SES and child zBMI.^42^ We will apply block randomisation (4 or 6) to ensure group allocation is approximately equal. Randomisation will be performed using R (V.4.3.2) and completed by an independent statistician following baseline data collection.

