#### ECEC service outcomes

Comprehensive nutrition and breastfeeding policies. ECEC services will be asked to provide any infant and toddler nutrition/healthy eating or breastfeeding policies they adhere to. Policies will be reviewed and assessed for content from the NHMRC infant feeding guidelines,^14^ a statement of support for breastfeeding provided at first contact with families, documented feeding plans, responsive feeding practices and educator training.Educator infant and responsive feeding practices. Five items based on the adapted Environment and Policy Assessment and Observation (EPAO) tool^60^ exploring the frequency of a range of infant feeding practices for children aged 2 years and under will be asked to one nominated educator within the infant room. These practices are related to bottle feeding, using bottles or food to soothe children, encouraging children over 6 months to drink from a cup and use age-appropriate cutlery, as well as progressing food textures appropriately. They will be rated on a 7-point Likert scale from never to always. The educator will also be asked 14 questions exploring responsive feeding: (1) education/modelling (three items), (2) using food as a reward (four items), (3) mealtime environment (three items) and (4) use of coercive practices (four items). The items are rated on a 5-point Likert scale from never to always and are based on the Adapted About Feeding Children Strategies and Beliefs survey.^61^ The responses to each item will be summed to provide an overall score, as well as a score for each construct. At follow-up only, we will also undertake researcher observations during a main mealtime, where most children are present (typically lunch) to assess delivery of the targeted feeding practices using an adapted version of the EPAO previously employed by the research team.^62^

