### Sample size calculation

The sample size calculation was based on the primary outcome, zBMI. Based on our previous study,^55^ the SD is approximately 1.0 and mean zBMI is approximately 0.41. To detect a clinically meaningful change in population zBMI of 0.26 (69) with 80% power (two-sided α=0.05, intracluster correlation coefficient=0.02), we will need to recruit 540 caregiver–child pairs (270 per group) from 60 ECEC services. As an intention-to-treat analysis will be undertaken as the main analysis (participants analysed according to allocation group), we will not account for attrition.

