### Statistical analysis

The primary analyses will be undertaken using an intention-to-treat approach, using multiple imputation to account for missing data. For the primary outcome (continuous zBMI), between-group differences at follow-up will be assessed using hierarchical linear regression models. We will also dichotomise the data to assess overweight/obese (zBMI using WHO cut-offs)^67^ and compare this using a logistic regression. All models will be adjusted for ECEC service-level clustering through a random effect and controlled for baseline measures and ECEC service SES and any other identified baseline imbalances. To assess differences between groups for secondary outcomes, linear regression analyses will be conducted (for continuous outcomes). Models will be adjusted for ECEC service-level clustering and any stratified variables through a random effect and controlled for baseline measures and ECEC service SES. Similar analysis will be undertaken for child-level secondary outcomes. All model inference will be conducted within the Bayesian framework. Sceptical, mean-centred normal prior distributions will be specified for the treatment effect and other fixed-effect regression parameters. A half-Student-t distribution will be used to model the SDs of random effects and residuals. Posterior draws will be obtained using the No-U-Turn Sampler, as implemented in the brms package for R.^68^ The probability of a favourable treatment effect (ie, the posterior probability that the treatment effect is greater than zero) will be reported, along with 95% credible intervals for the treatment effect parameters.

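### The secondary-outcome model makes the two binary stratifiers random effects, lists SES twice, gives single-record educator scores a service random effect, and omits child age

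*Protocol article*

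**What the plan says.** Under Randomisation, services are stratified by two dichotomies: whether Aboriginal and Torres Strait Islander enrolments reach 10%, and SES, "dichotomised as high/low SES according to the SEIFA classification" of the service postcode.

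Under Statistical analysis there are two model sentences. The first follows the primary outcome. It uses a random effect for service alone, with the baseline measure, service SES and any baseline imbalances found as covariates; the enrolment stratifier is not named. The second, for secondary outcomes, says the models are "adjusted for ECEC service-level clustering and any stratified variables through a random effect and controlled for baseline measures and ECEC service SES". It is followed by "Similar analysis will be undertaken for child-level secondary outcomes", so the model just described is meant for service-level outcomes as well as child-level ones. SDs of random effects and residuals have half-Student-t priors, and fixed effects have sceptical normal priors. The article gives no scales for them.

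Under ECEC service outcomes, the infant-feeding items "will be asked to one nominated educator within the infant room", and the same educator answers the responsive-feeding items. Each service therefore has one survey score at follow-up, with the baseline score used as a covariate.

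Child age is not named as a covariate in either sentence. Eligibility is 4 to 12 months at recruitment.

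**The concern.** Four features of the stated model deserve a second look.

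- **Two-level random effects.** A variance cannot be learned from two levels, so the prior supplies most of it.
- **SES twice.** SES is one of the stratifiers, so the literal text enters it once as random and once as a covariate. If both are coded high/low, the data inform only the sum of the two terms.
- **Service intercept with one record per service.** Service variance and residual variance are then the same thing to the data.
- **No child age.** Breastmilk duration and diet change quickly over the entry age range. Baseline breastmilk duration in completed months cannot exceed the child's age, so the baseline value is an imperfect stand-in for age.

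At stake are parameters that cannot be interpreted, possible sampling difficulty that would have to be resolved after data are seen, and some lost precision. Whether the treatment effects themselves are at stake needs checking.

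**Working it through.** **1. The plan's own figure.** The Sample size calculation gives "80% power (two-sided α=0.05, intracluster correlation coefficient=0.02"), a "clinically meaningful change in population zBMI of 0.26", "the SD is approximately 1.0 and mean zBMI is approximately 0.41", and "540 caregiver–child pairs (270 per group) from 60 ECEC services".
- Individually randomised: 2 × ((1.960 + 0.842)/0.26)² = 232.2 per arm.
- Cluster size 540/60 = 9; design effect 1 + (9 − 1) × 0.02 = 1.16.
- 232.2 × 1.16 = 269.4, so 270 per arm and 540 in total. Power at 270 per arm is 80.1%.

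The figure reproduces, and nothing below alters it. It fixes the scale: about 60 records for a one-per-service outcome.

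**2. Variance from two levels.** With 1 degree of freedom, s²/σ² follows a chi-square on 1 df. The 95% interval for σ runs from s/√5.02 = 0.45s to s/√0.00098 = 31.9s, even if the two level effects were observed without error.

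**3. SES twice, and one record per service.** For service j the literal model is y_j = α + β·treatment + γ·baseline + δ·SES + a(SES) + b(enrolment) + u_j + e_j.
- The SES contrast is δ + a(1) − a(0). Only this sum is informed by the data.
- With one record per service, Var(u_j + e_j) = τ² + σ². Only this sum is informed.

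A Bayesian linear model was fitted by importance sampling to one simulated dataset of 60 services with one record each. Assumed, because the article gives no scales: half-t(3, 0, 2.5) on SDs, N(0, 1) on slopes, 30 services per arm, SES split 24/36, enrolment split 40/20, generating effects 0.3 (treatment), 0.3 (SES), 0.5 (baseline) and residual SD 0.85. Entries are posterior mean (SD), or a 95% interval for SDs.

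| Model | Treatment | SES coefficient | Random-effect SD | Residual SD |
|---|---|---|---|---|
| SES fixed only | 0.359 (0.188) | 0.462 (0.193) | none | 0.61 to 0.88 |
| + service intercept | 0.359 (0.188) | 0.462 (0.193) | service 0.04 to 0.81 | 0.05 to 0.82 |
| + SES random as well as fixed | 0.360 (0.188) | 0.221 (0.723) | SES 0.04 to 3.89 | 0.62 to 0.89 |
| As written (SES, enrolment and service random, SES also fixed) | 0.365 (0.180) | 0.214 (0.736) | SES 0.05 to 4.05; enrolment 0.09 to 4.16; service 0.04 to 0.78 | 0.05 to 0.79 |
| Both stratifiers fixed once, no service intercept | 0.365 (0.180) | 0.471 (0.185) | none | not recorded |

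The second row shows the ridge: the median service and residual SDs were 0.45 and 0.56, and √(0.45² + 0.56²) = 0.72, close to the single residual median of 0.73 in the first row. In the last two rows the posterior SD of the SES coefficient is about four times larger as written (0.736/0.185 = 4.0), while the treatment effect agrees to three decimals.

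**4. Child age.** Entry at 4 to 12 months plus 18 months gives follow-up ages of about 22 to 30 months. If age explains a share R² of residual variance, adjusting for it multiplies the standard error by √(1 − R²). The documents give no R².
- R² = 0.05: 1 − √0.95 = 2.5% narrower.
- R² = 0.10: 1 − √0.90 = 5.1% narrower.
- Wider range, partial correlation 0.1, 0.2, 0.3, 0.4, 0.5: 0.5%, 2.0%, 4.6%, 8.3%, 13.4%.

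**The case against.** The sentence can be read more kindly. The singular random effect, and the preceding sentence that gives one to service only, allow the reading that the stratifiers are simply adjusted for. Nor does the article say that the SES covariate uses the same high/low coding as the stratifier. Both points stand as doubts about intent. They do not rescue the wording, which on its plain grammar puts the stratifiers in the random part and still names SES twice.

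The stronger objection is that no reported result changes. The article reports the probability of a favourable treatment effect and credible intervals for treatment effects; stratum variances and the SES coefficient are nuisance terms. This largely stands, and it rules out some tempting inferences. A reader might conclude that the secondary treatment effects are biased or their intervals wrong; the check shows neither. A reader might also expect the No-U-Turn Sampler to fail. It was not run here, and proper priors keep the posterior defined, so difficulty is possible but not demonstrated. Shrinkage of the stratum effects is no separate fault, since fixed effects also carry sceptical priors.

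The single-record point is secure only for the educator survey. The article does not say how many records the follow-up mealtime observations yield, or that policy content is scored as a continuous outcome.

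On age, a reader might call the omission an error or a source of bias. Services are randomised, so it is neither: it costs precision only. The baseline value carries part of the age effect, and the first model sentence, which speaks of all models, would admit age if it were found imbalanced. That route depends on the data, however, and the secondary-outcome sentence does not repeat it.

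**Conclusion.** The concern holds as a fault of stated specification with small consequences. Taken literally, the secondary-outcome model contains two variances resting on 1 degree of freedom each, a duplicated SES term and, for educator survey scores, a service variance inseparable from the residual. Those parameters would be governed mainly by their priors and could not be interpreted. The treatment estimate and its posterior SD were essentially unchanged (0.365, SD 0.180 as written and as corrected). That rests on one simulated dataset and assumed prior scales, although the two identification arguments do not depend on either.

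Leaving out child age loses a modest amount of precision, 2.5 to 5% of interval width under the assumed 5 to 10% of residual variance, and introduces no bias. Naming it is an improvement to a covariate list that the article does state.

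The change is worth making because it costs almost nothing and spares the analyst from choosing which terms to drop once data are in hand.

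**What to change.** Reword the two model sentences under Statistical analysis so that:
- both randomisation stratifiers (SES and the enrolment category) enter once each as fixed effects in every model, including the primary model, which at present names only SES;
- the service random intercept is used only for outcomes with several records per service, such as child and caregiver outcomes, and is dropped for educator survey scores and any other outcome with one record per service;
- child age is a fixed covariate for child and caregiver secondary outcomes. It must be recorded already, since both eligibility and zBMI depend on it.

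The cost is wording and model code. No new data are needed and the sample size is unaffected.

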## Ethics and dissemination

### Human research ethics approval

The trial was prospectively registered with the Australian New Zealand Clinical Trials Registry (ACTRN12624000576527). Ethics approval has been provided by Hunter New England (HNE) Human Research Ethics Committee (HREC) (2023/ETH01158), Deakin University (2024-202) and University of Newcastle HREC (R-2024-0039). Any changes to the approved protocol will be documented and submitted as formal amendments to the HREC.

### Privacy and confidentiality

Only research staff directly involved in the study will have access to identified participant data. Data will be deidentified using study ID numbers. Personal identifiable information (names, contact details) will be kept separately from outcome data and will be accessible only by research personnel.

### Patient and public involvement

We co-designed the Tiny Bites programme with the following interest-users (caregivers of young children attending ECEC services, health promotion teams, ECEC managers and ECEC educators), who were also consulted prior to development of the funding application. Most of the intervention materials were pilot tested with consumers prior to delivery and we drew on co-design workshops with ECEC providers, health care professionals and cargivers undertaken as part of the Grow and Go design (led by HT and CD). The health service delivery (HNELHD) and state health department who funds implementation support for ECEC services (NSW Centre for Population Health) are partners on the funding application and authors on this protocol.

### Dissemination plan

The results of this trial will be published in a peer-reviewed journal and presented at academic conferences/seminars. Results will be presented in a variety of formats including, but not limited to, conference abstracts, posters or presentations, seminars, journal articles and internet postings.
